### Randomization

Patients are randomly assigned to either the standard PSL plus high-dose mizoribine combination, or standard PSL alone group in a 1:1 ratio. We use a minimization method stratifying by age (2–5 years or 6–10 years), sex, duration from initial remission to relapse (< 90 days or ≥ 90 days) and institution as adjustment (stratification) factors. Patients, their guardians, treating physicians, and individuals assessing outcomes and analyzing data are not blinded to the patients’ treatment assignments. Apart from the trial statistician and the data-monitoring committee, all treating physicians and other investigators remain blinded to the trial results until follow-ups are completed.

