### Procedures

For the standard PSL plus high-dose mizoribine group, mizoribine is administered at a dose of 10 mg/kg/day (maximum 300 mg/day) once daily after breakfast and continued for 2 years. Mizoribin is started within 7 days from the registration date. After 2-year administration or termination of this trial, dosage of mizoribine will be tapered every month and stopped within 3 months. In case of leukocytopenia or impaired renal function, mizoribine treatment will be tapered or stopped. PSL treatment for relapse during the observation period follows the ISKDC regimen.

The observation period is from the registration date to the completion or discontinuation date of this trial. Completion of study is defined as completing of 2-year administration. Patients who complete or discontinue this study will be followed-up.

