### Outcomes

The primary endpoint is defined as the duration from registration to diagnosis of FRNS. Diagnosis of FRNS is based on relapse dates according to the ISKDC. In our study, FRNS is defined as two relapses within 6 months of initial remission, or four relapses within any 12-month period. This includes relapses during initial tapering treatment, but excludes relapses with spontaneous remissions. Relapse is defined as proteinuria 2+ or higher on dipstick analysis for 3 or more consecutive days or proteinuria 2+ or higher on dipstick analysis and serum albumin ≤2.5 g/dL. Immunosuppressant administration is prohibited in the protocol. If patients show SDNS or SRNS, they are treated as an event in the primary analysis. Data for patients who do not experience these events are considered censored at the last examination. Secondary endpoints are relapse-free period, the poportion of patients without relapses, the number of relapses per person/year, time to SDNS, time to SRNS, total prednisolone dose, and adverse events. Adverse events were recorded throughout the trial period and assessed using Common Terminology Criteria for Adverse Events v3.0. Serum mizoribine concentrations at trough and C3 are measured 1 month after administration of mizoribine to monitor safety and pharmacological effect.

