### Statistical analyses

The primary analysis of this study is to examine the superiority of PSL plus high-dose mizoribine combination therapy compared to standard PSL alone therapy in the time to FRNS.

For the sample size determination, we based the hazard rate ratio (HR, the PSL plus high dose mizoribine treatment group to the PSL treatment group) on the two-year FRNS probability. We estimated 50% at two-year in the standard PSL treatment and postulated the HR of 0.50. The required sample size was calculated as 108 patients (54 per arm) under a two-sided alpha 5% and 80% power, if the patients accrued for 4 years and follow up for 2 years. Considering withdrawal of consent or loss, target sample number was determined as 120 cases (60 each). We used POWER procedure of SAS software (version 9.3) for this calculation.

The primary endpoint, time to FRNS will be compared between these two groups using log-rank test. Cox proportional hazard model is used to estimate the hazard ratio with a 95% confidence interval. Kaplan-Meier method is used to summarize time to FRNS. The statistical significance level is set to 5%.

Secondary endpoints of relapse-free period and duration shifting to SDNS or SRNS will be compared in a similar manner as primary endpoint. The proportion of patients without relapses will be compared by Fisher’s exact test. Number of relapse and total steroid dose will be analyzed by Wilcoxson test. Correlation between mizoribine dose and blood concentration of mizoribine will be evaluated by Spearman rank correlation coefficient analysis.

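### The relapse endpoint is defined per person-year but its test is specified on the number of relapses, and neither it nor total steroid dose is given a time basis although observation can end early

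*Protocol article*

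**What the plan says.** Three places in the protocol article bear on this.

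- **Outcomes** lists among the secondary endpoints "the number of relapses per person/year, time to SDNS, time to SRNS, total prednisolone dose, and adverse events". Relapses are thus a rate; prednisolone is a total, with no unit and no period.
- **Statistical analyses** specifies: "Number of relapse and total steroid dose will be analyzed by Wilcoxson test". No denominator, offset or period is named.
- **Procedures** sets each child's time under observation: "The observation period is from the registration date to the completion or discontinuation date of this trial". It adds "Completion of study is defined as completing of 2-year administration", so completers share a nominal two years and the others have less. The same paragraph says that both completers and children who discontinue are followed further. It does not say what is recorded then, or whether it enters these analyses.

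**The concern.** A rank test on counts treats a short record as a good record. A control child relapsing at 1.5 per year (an assumed rate) expects 1.5 × 2 = 3 relapses over two years, but 1.5 × 0.5 = 0.75 if observed for six months. A mizoribine child with a 40% lower rate, observed in full, expects 0.9 × 2 = 1.8. On counts, the control child who left early tends to rank better. The same holds for a steroid total summed to the last day of observation.

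Less steroid exposure is the patient benefit that the article's Discussion expects, so these endpoints will be read closely. Early stopping could be unequal in either direction. Procedures has mizoribine tapered or stopped for leukocytopenia or impaired renal function, which can arise in one arm only. Outcomes prohibits immunosuppressants, so control children who reach FRNS might leave more often. If control children leave more, the benefit is understated; if mizoribine children leave more, it is overstated.

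**Working it through.** **The plan's own figure.** The article gives no figure for these endpoints. Its one calculation is for the primary test: "We estimated 50% at two-year in the standard PSL treatment and postulated the HR of 0.50", two-sided 5%, 80% power, 4 years' accrual and 2 years' follow-up. The Schoenfeld formula gives 4(1.960 + 0.842)² / (ln 0.5)² = 65.3, so 66 events. With hazards ln 2 / 2 and half of that, and uniform accrual, the event probabilities are 0.730 and 0.490, mean 0.610. Then 66 / 0.610 = 108, as stated, and 108 / (1 − 0.10) = 120. The implied loss is 10%, although no rate is stated. Nothing below changes these figures.

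**Inputs for the check.** From the article: 60 per arm, 1:1 allocation, nominal two years. Assumed, because the article gives none of them: control rate 1.5 to 2.5 relapses per year, gamma-Poisson variation with dispersion 0.5, true rate ratio 1 (for type I error) or 0.6 (for power). Early stoppers leave at a uniform time between 0.1 and 2 years (mean 1.05), regardless of their relapses.

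**Why counts drift.** With 50% of controls and 10% of mizoribine children stopping early, mean follow-up is 0.5 × 2 + 0.5 × 1.05 = 1.525 years against 0.9 × 2 + 0.1 × 1.05 = 1.905 years. With equal rates of 1.5 per year, mean counts are 2.29 and 2.86: control looks 20% better with no true difference. With a true ratio of 0.6, the count ratio is 0.6 × 1.905 / 1.525 = 0.75.

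**Wilcoxon test on counts and on per-child rates** (control 1.5 per year, 3,000 replicates; Monte Carlo standard error at most about 1 point):

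| Early stopping, control / mizoribine | Type I error, counts | Type I error, rates | Power, counts | Power, rates |
|---|---|---|---|---|
| none, all 2 years | 4.5% | 4.5% | 74% | 74% |
| 10% / 10% | 5.3% | 5.6% | 69% | 70% |
| 30% / 30% | 4.2% | 4.3% | 63% | 66% |
| 50% / 30% | 9.6% | 5.8% | 35% | 56% |
| 50% / 10% | 27.6% | 6.5% | 19% | 52% |
| 10% / 30% | 10.6% | 5.1% | 86% | 76% |

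In the last row the higher power on counts is bias in favour of mizoribine, not a gain.

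**If observation ended at FRNS** (an assumption; only the criterion of four relapses in 12 months is modelled, with the relapse that led to entry counted as one of the four; 1,500 replicates, true ratio 0.6):

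| Control rate per year | Mean counts (ratio) | Relapses per year observed (ratio) | Power, counts | Power, rates |
|---|---|---|---|---|
| 1.5 | 2.15 vs 1.56 (0.73) | 1.29 vs 0.84 (0.65) | 63.4% | 71.5% |
| 2.0 | 2.44 vs 1.89 (0.77) | 1.61 vs 1.08 (0.67) | 60.7% | 74.5% |
| 2.5 | 2.63 vs 2.15 (0.82) | 1.92 vs 1.29 (0.67) | 52.2% | 79.5% |

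Type I error stays near 5% for both, because with no treatment effect the arms reach FRNS equally often. The harm here is attenuation and lost power, about 8 to 27 points. Dividing by time removes most of the attenuation but not all of it: 0.65 to 0.67 against a true 0.6.

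**The case against.** The strongest reply is that Statistical analyses restates several secondary endpoints loosely, so the number of relapses may be shorthand for the per-person-year endpoint. A Wilcoxon test on each child's rate would satisfy both sections. This stands as a possible reading. A reader might infer that raw totals are definitely planned; the article does not say so. It does, however, name two different variables, and only the sponsor can say which is meant.

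Four further limits also stand.

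- The mismatch concerns relapses only. The steroid endpoint is defined as a total and analysed as a total; what it lacks is a stated period.
- A reader might treat missing scaling of dose to body size as an error. No unit is given at all, and an article may leave that to the full protocol. With allocation in a "standard PSL alone group in a 1:1 ratio" and age band and sex among the minimization factors, body size mainly adds noise.
- A reader might infer that observation stops at FRNS. Procedures ends it at completion or discontinuation and promises further follow-up, so the second table is conditional. The loss also depends on how FRNS is counted. In a separate run (54 per arm, rate ratio 0.5, 1.5 per year), power on counts fell from full follow-up by about 8 points when the entry relapse counted towards the four and by about 3 when it did not. At 2 per year the losses were about 17 and 9.
- At 10% balanced loss, the level implied by going from 108 to 120, counts and rates barely differ. The article gives no sign of how far stopping will differ by arm.

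**Conclusion.** The point holds as an inconsistency in how a secondary endpoint is specified, plus an unstated time basis for steroid dose. Its consequence is conditional. It is negligible with complete follow-up or about 10% balanced stopping. Under the arm-differential stopping patterns simulated, type I error on counts is about 10–28%, with bias in either direction. If observation ended at FRNS, the cost is about 8 to 27 points of power. These sizes rest on assumed relapse rates, dispersion, effect and stopping patterns, none of which is in the article.

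The finding does not extend to the log-rank comparison of time to FRNS or to the sample size. It is a cheap improvement to secondary endpoints, worth making because the remedy is specific and removes a choice that could otherwise be made after the data are seen.

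**What to change.** 1. Name the relapse variable identically in Outcomes and Statistical analyses, as relapses per person-year.
2. Analyse it with a negative binomial model, log link, log follow-up time as offset, and report the rate ratio with its 95% confidence interval. At minimum, apply the Wilcoxon test to per-child rates. The model is preferable because it gives an effect size and weights each child by time observed.
3. Define the steroid endpoint as cumulative prednisolone over the 24 months from registration in both arms, including data after FRNS and after mizoribine has been stopped. The Wilcoxon test can stay. State how children not observed to 24 months are handled.
4. Use the same post-FRNS and post-discontinuation data for the relapse rate, since an offset alone does not fully correct stopping that depends on relapses.
5. State the unit of the steroid dose. Scaling to body size would be a subsidiary gain in precision.

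The cost is a change of analysis wording, slightly more analysis work, and reliance on relapse and prednisolone records after discontinuation. Procedures already promises that follow-up, but the sponsor should confirm that these items are recorded in it. No change in sample size is needed.

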## Discussion

The purpose of this trial is to examine efficacy and safety of high-dose mizoribine in preventing patients with NS who show an early relapse within 6 months after initial remission from shifting to FRNS. One of most noteworthy adverse events in patients with SSNS is harmfulness of steroids, especially to those with FRNS/SDNS. It has been clarified that prolonged ISKDC steroid regimen for patients with SSNS did not shorten the relapse-free period [2, 14–16]. It is therefore reasonable to pursue new strategies to prevent patients with SSNS from shifting to FRNS. Although immunosuppressants are considered as second-step drugs next to steroids, use of them should be carefully decided due to severe side effects. Under such a condition, it is important to recognize predictive risk factors for FRNS. Previously, we clarified that a relapse within 6 months after initial treatment for NS is a predictive risk factor for FRNS [2]. Development of an optional drug regimen for patients who have such a risk factor is therefore desirable. From this perspective, we focused on mizoribine and conducted a randomized controlled trial to examine efficacy and safety of adding optional mizoribine to patients with NS.

Mizoribine has been developed in Japan. It is an imidazole-based nucleic acid-related substance derived from the culture fluid of *Eupenicillium brefeldianum.* Mizoribine is an antimetabolite to inhibit the purine synthesis pathway of nucleic acids, it shows an immunosuppressive effect of more selectively inhibiting lymphocyte proliferation [17, 18]. Unlike other immunosuppressive drugs, such as cyclosporine and cyclophosphamide, toxicity and myelosuppression of mizoribine seems to be milder. Mizoribine is also considered to have an effect to enhance glucocorticoid efficacy [19].

Historically, mizoribine has been used to suppress rejection reactions in kidney transplantation [20, 21], lupus nephritis [22, 23] and rheumatoid arthritis. Mizoribine has also been reported to be effective as a treatment for IgA nephropathy [24, 25]. It is approved as a treatment of NS in Japan [3, 26]. By adding mizoribine, the total dose of steroids can reportedly be reduced in treatment for NS. [27]. Furthermore, a double-blind, placebo-controlled, multicenter trial has shown that mizoribine significantly decreased relapse rate and prolonged remission period in children with FRNS in the subgroup consisting of patients 10 years old or younger [3]. Although efficacy and safety of mizoribine are well recognized in medical practice, blood concentration of mizoribine has not always been sufficient to reach efficacy. There is therefore a possibility that mizoribine is underestimated compared to other immunosuppressive drugs. Conventional use of mizoribine (3–4 mg/kg daily, maximum 150 mg/day) leads to a peak blood level at around 1.0 μg/mL [5], although a peak blood level of 2.5–3.0 μg/mL is biologically required to sustain long-term efficacy for the treatment of glomerular diseases [6, 7]. Consequently, high-dose mizoribine administrations aiming to retain high serum mizoribine concentration have come to be considered for children with FRNS [12, 13]. Serum C2 concentrations are known to be around 3 μg/mL in patients who achieved decrease in the number of relapses by taking 10 mg/kg/day of mizoribine once a day without severe side effects. Therefore, in the current protocol, we adopted dosage of 10 mg/kg/day of mizoribine once a day (maximum 300 mg/day).

If we can prevent at-risk patients from shifting to FRNS by adding high-dose mizoribine effectively and safely, we will reduce the total dose of steroids for patients, resulting in less side effects. Moreover, we will avoid use of other immunosuppressants, such as cyclosporine and cyclophosphamide, which are proven to be more effective but have more serious side effects than mizoribine. Patients with mizoribine treatment do not require frequent blood tests or renal biopsy, which is seen as a great benefit. As a result, it is expected to reduce medical expenses despite cost of mizoribine.

## Summary

The present study aims to examine efficacy and safety of standard PSL plus high-dose mizoribine therapy used to prevent at-risk children with SSNS from shifting to FRNS. An early relapse within 6 months after initial remission in patients with SSNS is a definitive risk for the shift to FRNS. High-dose mizoribine administration promises biological and clinical bases for efficacy. These conditions give the protocol strong rationales. The results of this trial may be of great benefit to children with SSNS at risk of FRNS and to their families.

## Abbreviations

FRNS: frequently relapsing nephrotic syndrome
ISKDC: International Study of Kidney Disease in Children
NS: nephrotic syndrome
PSL: prednisolone
SSNS: steroid sensitive nephrotic syndrome
